## Abstract

**Introduction:**

Prostate cancer (PCa) represents a major global health concern due to biological heterogeneity and the complexity of its underlying molecular pathways, which contribute to substantial morbidity and mortality. Ongoing research continues to elucidate distinct molecular mechanisms that may inform diagnostic and therapeutic strategies. Among these, the prostate-specific membrane antigen (PSMA) has emerged as a pivotal biomarker and therapeutic target in PCa. PSMA is indirectly modulated by androgen signalling through the androgen receptor (AR) pathway and has been observed to undergo transient upregulation following treatment with AR targeting agents, such as darolutamide, particularly in patients with castration-resistant PCa. This transient increase in PSMA expression—termed the ‘PSMA flare phenomenon’—may enhance the sensitivity and accuracy of PSMA-based molecular imaging and disease staging.

**Methods and analysis:**

The DARO-flare trials are a prospective, single-centre, interventional, phase I–II proof-of-concept study evaluating whether short-term administration of darolutamide induces a PSMA-flare in patients with hormone-sensitive PCa. The cohort being investigated comprises patients with oligometastatic recurrence following prior therapy with curative intent.

Within the cohort, participants are randomised (1:1) to receive darolutamide 600 mg two times a day for either 7 or 14 days. All participants undergo baseline PSMA positron emission tomography (PET)/CT imaging as standard-of-care and two follow-up scans on days 7 and 14.

The primary endpoint was the change in the number of PSMA-expressing PCa lesions and/or PSMA expression per lesion maximum standardised uptake value on repeated PSMA PET/CT, indicative of a darolutamide flare response. Secondary endpoints included the impact on clinical management decisions, defined as a treatment change following short-course darolutamide, tolerability and toxicity as assessed by adverse event reporting, and patient-reported outcomes related to quality of life.

**Ethics and dissemination:**

The study protocol has been approved by the Medical Ethics Committee (METC) Amsterdam UMC and adheres to the Declaration of Helsinki. Written informed consent is obtained from all participants. Study findings will be disseminated through peer-reviewed publications and conference presentations.

**Trial registration number:**

2025-520482-52-03 (https://euclinicaltrials.eu/ctis-public/view/2025-520482-52-03?lang=en, protocol nr 6.0).

STRENGTHS AND LIMITATIONS OF THIS STUDYThis is a prospective single-centre phase I–II interventional study using a randomised design between two exposure durations.Serial prostate-specific membrane antigen (PSMA) positron emission tomography/CT imaging at three predefined timepoints enables evaluation of temporal kinetics of PSMA upregulation.Imaging interpretation is based on standardised PSMA PET/CT Analysis and Reporting Consensus (SPARC) criteria and dual-reader assessment.The study is limited by its small sample size and exploratory, non-confirmatory design.The single-centre design may limit the generalisability of the findings.

## Introduction

 Prostate cancer (PCa) remains a major global health concern, characterised by its biological heterogeneous nature and complex androgen-dependent signalling pathways. The prostate-specific membrane antigen (PSMA), a transmembrane glycoprotein highly expressed in malignant prostate tissue, has emerged as a promising theranostic target, serving both diagnostic and therapeutic applications.

PSMA is indirectly regulated through the androgen receptor (AR) pathway. Under normal physiological conditions, androgens such as testosterone are converted to dihydrotestosterone (DHT), which forms a DHT-AR complex that suppresses the folate hydrolase 1 (*FOLH1)* gene, thereby reducing PSMA protein synthesis. Inhibition of this signalling by androgen receptor targeting agents (ARTAs), including darolutamide, enzalutamide and apalutamide, reverses this suppression mechanism and results in upregulation of PSMA expression, a phenomenon referred to as the ‘flare phenomenon’.^1^

The PSMA-flare phenomenon, characterised by enhanced PSMA protein expression, holds promise for improving PCa imaging and therefore staging. Preclinical studies using human PCa cell lines, such as LNCaP and C4-2, have demonstrated concentration-dependent PSMA upregulation on exposure to ARTAs.^1^,^8^ Furthermore, clinical evidence from human case reports and prospective studies corroborates these findings, with short-term ARTA treatment leading to increased maximum standardised uptake value (SUV_max_) on PSMA-positron emission tomography (PET/CT) imaging.^9^,^17^ The optimum timeframe for ARTAs to exhibit the flare phenomenon appears to range between 9 and 14 days.^13^,^16^ Interestingly, the flare phenomenon is confined to PSMA-expressing target organs and is not observed in organs-at-risk, which are responsible for potential side effects.^9^,^16^

Despite structural differences among ARTAs, their pharmacokinetic behaviour and AR antagonism are comparable, and it is reasonable to anticipate no alteration in their mechanism of action. Preclinical data suggest a consistent flare phenomenon across various ARTAs, with darolutamide demonstrating similar upregulation compared with enzalutamide.^8^

This study aims to investigate the effect of ARTAs, specifically darolutamide, on the upregulation of PSMA (the PSMA flare) in patients at various stages of hormone-sensitive PCa. The potential impact of this transient PSMA flare on molecular imaging modalities may contribute to more accurate disease detection and staging.

Enhanced staging precision could, in turn, inform treatment selection, optimise therapeutic planning and ultimately improve patient outcomes and quality of life.^18^

## Methods and analysis

### Study setting

This study represents a prospective, single-centre, interventional, phase I–II proof-of-concept study (2025–520482-52-03) conducted at Amsterdam UMC, location VUmc. The study is planned to start in January 2026 and is to be completed in December 2026. The following cohort is studied:

Patients with oligometastatic recurrence (≤5 lesions) after curative-intent therapy.

Within the cohort, patients are randomised (1:1) to receive darolutamide 600 mg two times a day for 7 or 14 days (open-label). PSMA PET/CT is repeated on days 7 and 14 for all patients.

### Population and eligibility criteria

The study population comprises patients diagnosed with PCa, with oligometastatic recurrence (≤5 lesions) detected on re-staging PSMA PET/CT following curative-intent treatments like robot-assisted radical prostatectomy (RARP) or external beam radiation therapy (EBRT). Baseline staging before definitive treatment was performed according to standard clinical practice. Histopathological characteristics, including histological subtype, are recorded in the electronic patient record.

Inclusion criteria require participants to be adult men (>18 years), with histologically confirmed PCa, an Eastern Cooperative Oncology Group performance status of 0–1, and a life expectancy exceeding 12 months. Patients must not have received prior hormonal therapy, must be able to understand the patient information form, and must have provided written informed consent. In addition, eligible patients must have previously undergone RARP or EBRT, and have a PSMA PET/CT demonstrating 1–5 metastatic lesions in bones and/or lymph nodes, irrespective of prostate-specific antigen (PSA) level, grade or disease stage.

Exclusion criteria include non-adenocarcinoma histology, prior PSMA-based radioligand therapy, prior use of ARTAs within the preceding 3 months, presence of visceral or central nervous system metastases, concurrent cytotoxic chemotherapy, immunotherapy, radioligand therapy or investigational therapy, and other specified medical conditions that could impact trial participation (see Concomitant medication section). Additional exclusions include known hypersensitivity to darolutamide or related compounds, prior hip replacement surgery, Sjogren’s syndrome, the presence of second active malignancies or unwillingness to use medically acceptable forms of barrier contraception.

### Intervention

Darolutamide (Nubeqa) is administered orally at 600 mg two times a day with food for either 7 or 14 days, based on treatment arm. Treatment is followed by a 21-day follow-up period, during which two follow-up PSMA PET/CT scans with (^18^F)F-Piflufolastat (Pylclari) will be performed in an outpatient setting.

### Concomitant medication

Any medication that is considered necessary and will not interfere with the study medication or its outcomes may be given at the investigator’s discretion. Other (anti)androgenic treatment may influence the flare phenomenon and are not allowed during the study period. Darolutamide is a substrate for cytochrome P450 (CYP) 3A4, P-glycoprotein (P-gp), breast cancer resistance protein (BCRP) and uridine diphosphate-glucuronosyltransferase (UGT) 1A9. The drug inhibits BCRP, organic anion transporting polypeptide (OATP) 1B1 and OATP1B3 and is a small inducer of CYP3A4. The use of strong CYP3A4 inhibitors may increase the systemic exposure to darolutamide and are therefore prohibited. Likewise, strong CYP3A4 inducers may decrease the exposure of darolutamide. All other concomitant treatments will be registered in the eCRF.

### Criteria for defining the flare phenomenon

The flare phenomenon is defined as follows (table 1): a PSMA flare is identified by the appearance of at least one new PSMA-expressing lesion as compared with baseline imaging, using a liver uptake-specific threshold, according to the Standardised PSMA PET/CT Analysis and Reporting Consensus (SPARC) reporting consensus.^19^ These new lesion(s) may represent either local recurrent disease or new metastatic deposits. Additionally, a PSMA-flare phenomenon can be defined as a clinically significant increase in SUV_max_ and mean standardised uptake value (SUV_mean_) of pre-existing lesions, defined as ≥20%, relative to baseline PSMA PET/CT. Finally, progression from oligometastatic to poly-metastatic disease on repeat PSMA PET/CT. Poly-metastatic disease is defined as the presence of more than five lymph node or bone metastases on follow-up imaging, compared with ≤5 lesions on baseline PSMA PET/CT.

**Table 1 T1:** Overview of PSMA flare criteria in the patient cohort

Baseline PSMA PET/CT	PSMA flare criteria
Oligometastatic (≤5 lesions)	≥1 new PSMA-positive lesion with SUV_max_ and SUV_mean_ >liver uptake-specific threshold ≥20% increase in SUV_max_ and SUV_mean_ of existing lesions New lesions may be local recurrence or metastases Conversion from oligometastatic (≤5 lesions) to poly-metastatic (>5 lesions) disease

PET, positron emission tomography; PSMA, prostate-specific membrane antigen; SUVmax, maximum standardised uptake value; SUVmean, mean standardised uptake value.

### Objectives

The primary endpoint was to prospectively investigate whether the ‘darolutamide flare phenomenon’, observed after the administration of the second line ARTA darolutamide in patients with PCa, results in (1) a higher number of PSMA expressing PCa deposits, either defined as local residual disease or metastatic disease, or (2) in a higher expression of PSMA in individual lesions, determined by SUV_max_, on PSMA PET/CT.

The secondary objectives were (1) to assess the absolute number and the relative number of patients in whom a treatment change is observed by renewed imaging by PSMA PET/CT after a short (7 or 14 days) course of administration with darolutamide, and (2) to assess the patient-reported toxicity and side effects of a short course of administration with darolutamide.

### Sample size

A total of 16 patients will be enrolled, with eight participants per treatment arm (figure 1). The decision to include eight patients per study group is based on a confidence level of 95% and an estimated event probability of 32%, derived from prior studies reporting an average PSMA upregulation of approximately 40% (95% CI 1% to 110%). This sample size is pragmatic and aligns with typical early proof-of-concept oncology studies, focusing on biological feasibility rather than hypothesis testing. Data generated from this study will inform statistical powering of future randomised trials.

**Figure 1 F1:**

Flowchart of the study design. b.i.d., two times a day; PET, positron emission tomography; PSMA, prostate-specific membrane antigen.

### Data collection methods

#### PSMA PET/CT imaging

Patients will be staged with (^18^F)F-piflufolastat (Pylclari) which will be synthesised via direct radiofluorination under Good Manufacturing Practice conditions at an on-site cyclotron facility. Patients will receive 300±10% MBq of (^18^F)F-piflufolastat. PSMA PET/CT imaging will be performed according to local protocol on a European Association of Nuclear Medicine (EANM) Research Ltd. (EARL)-accredited total body PET system and in line with the EANM guidelines on PCa imaging.^19 20^ Protocol started with a low-dose CT scan (50 mAs, 120 kV), followed by a PET scan 120 min after injection. PET images will be acquired from mid-thigh to skull-base. To mitigate radiation exposure, all scans are performed using low-dose CT protocols and optimised PET acquisition according to As Low As Reasonably Achievable (ALARA) principles, and the cumulative exposure of three scans was reviewed and approved by the medical ethics committee as acceptable for this short-term study.

For each scan, PET data were reconstructed using the default blob ordered-subsets time-of-flight reconstruction algorithm, providing images with a matrix of 144×144×45 voxels and with an isotropic voxel size of 4 mm. All PET-images will be corrected for scatter, decay and random coincidences. The PSMA PET/CT scans will be interpreted by both a nuclear physician and an independent reviewer in line with the SPARC guidelines.^21^ Lesion number, location, SUV_max_, SUV_mean_, PSMA expression in the prostate, prostate bed or metastases (lymph node and/or bone metastases), and lesion reporting adhering to molecular imaging TNM classification as per SPARC criteria will be assessed.^21^ Visual and quantitative assessments will be provided, detailing suspected cancer sites, location, size and number. Additionally, findings will be classified on a validated 5-point scale to indicate the likelihood of PCa presence.

#### Blood sample collection

Blood samples will be drawn at the outpatient department on day 0, as standard-of-care, including evaluations of haemoglobin/haematocrit, creatinine, aspartate aminotransferase/alanine aminotransferase, alkaline phosphatase, PSA and testosterone levels.

#### Adverse event monitoring

Adverse events (AEs) and serious AEs (SAEs) are recorded from informed consent until end-of-study and graded per National Cancer Institute Common Terminology Criteria for Adverse Events (CTCAE V.5.0). Expected short-term side effects of darolutamide include mild fatigue and hot flushes (1%–10%).

#### Quality of life assessment

Quality of life will be assessed using quality of life questionnaires (patient-reported outcome measures) from the European Organisation for Research and Treatment of Cancer, at baseline and at end of follow-up.

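### No patient-reported measure is scheduled during dosing, although patient-reported toxicity of the short course is a secondary objective

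*Protocol article*

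**What the plan says.** All references are to the protocol article.

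- **Objectives.** The second secondary objective is "to assess the patient-reported toxicity and side effects of a short course of administration with darolutamide".
- **Quality of life assessment.** The questionnaires come "from the European Organisation for Research and Treatment of Cancer, at baseline and at end of follow-up". No other patient-reported instrument and no other time point is named.
- **Intervention.** Darolutamide is taken "for either 7 or 14 days, based on treatment arm". The section continues: "Treatment is followed by a 21-day follow-up period, during which two follow-up PSMA PET/CT scans" are made.
- **Study setting.** "PSMA PET/CT is repeated on days 7 and 14 for all patients".
- **Adverse event monitoring.** Adverse events "are recorded from informed consent until end-of-study and graded per National Cancer Institute Common Terminology Criteria for Adverse Events". Mild fatigue and hot flushes are named as expected short-term side effects, at 1%–10%.
- **Abstract, Methods and analysis.** The secondary endpoints are described differently there, as "tolerability and toxicity as assessed by adverse event reporting, and patient-reported outcomes related to quality of life" (besides the effect on management decisions).

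**The concern.** The objective is about what patients report while exposed to a short course. The instrument is applied once before the drug and once after it has stopped. The expected side effects are subjective symptoms, the kind a patient questionnaire is meant to pick up, and they may be gone by the only post-baseline form.

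At stake is how a null result is read. If quality of life at the end of follow-up matches baseline, that could be reported as good patient-reported tolerability, although nobody was asked while on drug. The Discussion gives favourable tolerability as a reason for choosing darolutamide, so a null finding would seem to confirm a premise that the questionnaire schedule did not test.

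The two time points are stated outright. This is a schedule that does not fit its own objective, and not a detail left to a fuller document.

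**Working it through.** The plan gives no figure on this point to reproduce. The check is day arithmetic on the stated schedule.

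**Inputs**
- Dosing length D: 7 or 14 days (Intervention).
- Follow-up length: 21 days (Intervention).
- Scan visits: days 7 and 14 in all patients (Study setting), taken as counted from the start of dosing.
- Patients: 16, eight per arm (Sample size).
- Recall period R of the questionnaires: not given. Assumed range 7, 14 and 28 days.

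**Step 1: when does follow-up end?** The Intervention section allows two readings. It says the 21 days come after treatment, and also that both follow-up scans fall within them. In the 14-day arm the day-7 scan is mid-course, so it cannot lie in a period that starts after the last dose. Both readings are therefore carried through.

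- Reading A, 21 days from the last dose: end day E = D + 21, which is 7 + 21 = 28 and 14 + 21 = 35.
- Reading B, 21 days from the first dose: E = 21 in both arms.

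**Step 2: days off drug at the last questionnaire, E − D**

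| Reading | 7-day arm | 14-day arm |
|---|---|---|
| A | 28 − 7 = 21 | 35 − 14 = 21 |
| B | 21 − 7 = 14 | 21 − 14 = 7 |

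Each patient has one post-baseline questionnaire, and it is never on drug. Under B the time off drug also differs between arms.

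**Step 3: could recall reach back into dosing?** Dosing days covered = max(0, D − max(0, E − R)).

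| Recall (assumed) | A, 7-day arm | A, 14-day arm | B, 7-day arm | B, 14-day arm |
|---|---|---|---|---|
| 7 days | 0 of 7 | 0 of 14 | 0 of 7 | 0 of 14 |
| 14 days | 0 of 7 | 0 of 14 | 0 of 7 | 7 of 14 |
| 28 days | 7 of 7 | 7 of 14 | 7 of 7 | 14 of 14 |

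A 7-day recall covers no dosing day in any case. A 14-day recall covers part of one arm under one reading. Of the periods tried, only 28 days reaches the 7-day arm at all, and under A it still covers only half of the longer course.

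**Step 4: what else covers the dosing days?** Adverse events are collected from consent to the end of the study, so they cover every dosing day. They are graded by CTCAE. The article does not describe this as a form that patients complete, and I take the grading to be done by study staff.

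**The case against.** The strongest reply is that toxicity is not the questionnaires' job. The abstract assigns toxicity and tolerability to adverse event reporting and keeps patient-reported outcomes for quality of life. Adverse events are recorded throughout dosing and can include symptoms that patients mention. A baseline-and-end schedule is a defensible choice for quality of life in a 16-patient proof-of-concept study with descriptive analyses.

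Much of this stands, and it limits what may be concluded. Three stronger readings are tempting, and the article does not support them:

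- *That the objective cannot be answered at all.* Adverse event data cover the dosing days, and the last questionnaire can show persisting effects or, with a long recall period, some of the dosing period.
- *That short-lived symptoms will have resolved by the last form.* The article gives no duration or recovery time for side effects and no recall period. They may have resolved; that they will have is not shown.
- *That a 7- versus 14-day tolerability comparison is spoiled.* The Objectives name no such comparison, and the Discussion ties randomisation to the timing of the flare. If the 1%–10% is read per side effect, eight patients per arm give 8 × 0.01 = 0.08 to 8 × 0.10 = 0.8 expected cases. The chance that none of 16 patients has a given effect is 0.99^16 = 0.85 at 1% and 0.90^16 = 0.19 at 10%. That comparison would say little under any questionnaire schedule.

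What the reply does not remove is the wording of the Objectives section, which specifies patient-reported toxicity. CTCAE-graded adverse events do not fully replace that, and the abstract and Objectives describe the endpoint differently.

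**Conclusion.** The concern holds in limited form. The only post-baseline patient-reported assessment falls 21 days after the last dose in both arms (reading A), or 14 and 7 days after it (reading B). During dosing, symptoms are captured only through adverse event reporting. The questionnaires may miss short-lived symptoms, and the patient-reported result could then lean toward no effect.

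The timing finding needs no outside assumption and is the same under both readings. Both the possibility and the size of the bias depend on recall period and symptom duration, which the article does not give, so no magnitude is claimed. The point concerns one secondary objective and leaves the primary endpoint and the sample size untouched. It is worth correcting because the mismatch is plain and the remedy is cheap.

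**What to change.** 1. Give the same questionnaires also at the day-7 and day-14 scan visits, which all patients already attend. At day 7 all 16 patients have had the same planned exposure. At day 14 one arm is finishing its course and the other has been off drug for 14 − 7 = 7 days.
2. Keep the end-of-follow-up questionnaire as a recovery assessment.
3. Summarise all time points descriptively, in line with the Statistical methods section.
4. Reconcile the second secondary objective with the abstract, so that it is clear which data answer the toxicity question and which answer quality of life.
5. Reconcile the Intervention section with the scan days in Study setting, and state whether the 21 days run from the first or the last dose.

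Cost: two extra questionnaires per patient, 16 × 2 = 32 in total, with a small added burden at visits already planned and an amendment to the schedule. Items 4 and 5 are wording changes only.

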#### Data management and confidentiality

A data management plan, adhering to the findable, accessible, interoperable and reusable (FAIR) principles, will be implemented following the guidelines of the Amsterdam University Medical Center Clinical Research Bureau (CRB). Restricted access to data will be enforced, and an electronic log will be maintained to track patients meeting eligibility criteria, those invited to participate, recruited patients and those who withdraw from the study, with reasons for non-recruitment documented. Reasons for withdrawal and failure to follow-up will also be documented during the study period. Data will be electronically stored in case report forms (CRFs) software equipped with audit trail functionality, subject to audit by the institutional CRB. The electronic CRF approved by Good Clinical Practice (GCP) standard will be sourced from Castor EDC (Castor EDC, Amsterdam, The Netherlands).

Each participant will be assigned a study code in the electronic CRF software based on application order for de-identification purposes. Only de-identified information will be stored, and participants will be identifiable solely by their unique study number, stored separately. Data will be retained on servers for 25 years in accordance with national guidelines, with the principal investigator granted access to the final trial dataset. Data generated in this study will be made available on reasonable request from qualified researchers, in accordance with institutional and ethical regulations. A data sharing plan has been submitted in the trial registry in line with International Committee of Medical Journal Editors requirements.

